Cost per additional ANC visit^a^	Cost-effectiveness ratio: effect on the second primary outcome divided by effect on the third primary outcome	Ratio	Quantitative household survey, MMHW dashboard
Financial distress^a^	Woman reporting at least one sign of financial distress	Binary variable	Quantitative household survey
Time to seek medical attention^a^	Time from first symptoms until professional medical care was accessed	Continuous time variable	Quantitative household survey
MMHW usage^a^	Woman who used the MMHW to pay for ANC or delivery-related expenses either in part or entirely	Binary variable	Quantitative household survey
Patient satisfaction^a^	Patient satisfaction with health facility and MMHW	Likert scale, qualitative interviews	Quantitative and qualitative household survey
Health system satisfaction^a^	Satisfaction with the health system	Likert scale, qualitative interviews	Quantitative and qualitative household survey
Life satisfaction	Satisfaction with general life situation	Likert scale, qualitative interviews	Quantitative and qualitative household survey
Time of sign-up	Time of sign-up to MMHW in relation to delivery date	Continuous time variable	Quantitative household survey, MMHW dashboard

^a^Pre-registered outcomes at DRKS (Deutsches Register Klinischer Studien, German Clinical Trials Register, identifier: DRKS00014928); *MMHW* maternal mobile health wallet, *ANC* antenatal care, *C-section* caesarean section

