### Conceptual framework and study objectives

We hypothesize that the implementation of a MM-based payment and savings service for maternal healthcare, the so-called Mobile Maternal Health Wallet (MMHW), will improve access to skilled care during pregnancy and childbirth by reducing financial obstacles. To test this hypothesis, we designed a hybrid effectiveness-implementation type-1 trial, called the Madagascar Mobile MOney for maTernal HEalthcare-Related Spending (4MOTHERS) trial, for evaluation of the MMHW in public-sector health facilities in the Analamanga region of Madagascar. Our trial complements the randomized implementation of the MMHW intervention by a non-governmental organization. The reason for facility randomization was to ensure procedural equality as the implementer’s funding constraints limited the number of facilities allocated to the intervention. The 4MOTHERS trial will adopt a multidisciplinary, cluster-randomized approach complemented by a process oriented mixed-methods evaluation to assess the impact of the intervention on (i) maternal and neonatal health outcomes, (ii) financial outcomes, and (iii) its feasibility, acceptability, and usefulness in the context of its implementation. More generally, the trial will contribute to our understanding of the health system impact of a digital tool for financial inclusion and access to essential healthcare services. In doing so, the trial will add to the scarce evidence on the usefulness of digital tools to achieve UHC. The evidence from this trial is important because it can inform governments in SSA on how to improve access to essential healthcare services, and maternal healthcare in particular, in public-sector healthcare systems.

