#### Analysis of the randomized controlled trial

Our primary analysis will be an intent-to-treat (ITT) causal effect estimation of our registered pre-specified primary and secondary outcomes. The effect sizes determined in the primary analysis provide an unbiased measure of the real-life policy impact of our intervention. As a secondary analysis, we will also conduct a contamination-adjusted intention-to-treat analysis (CA ITT) using an instrumental variable to adjust for bias [58]. For the CA ITT analysis, we will use the random assignment to intervention vs. control facility catchment area of this trial as an instrumental variable (IV) to measure the effect size that would have been attained without “contamination.” Contamination occurs when women who live in an intervention area do not utilize the MMHW and women who live in a control area utilize the MMHW to receive health care. The treatment in the IV analysis is participants’ actual MMHW registration status. The effect size determined in this secondary analysis provides a measure of the full effect that the intervention would have induced in the absence of intervention utilization (or lack thereof) that did not conform with the intervention status intended by the random assignment of geographical communities. We will regress the primary and secondary outcomes (Table 1) on the random assignment of participants to facility catchment intervention vs. control area. For our binary outcomes, we will use modified Poisson regression analysis [59]; for our count outcomes, we will use negative binomial regression; and for our continuous outcomes, we will use linear regression for effect size estimation.

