#### Economic evaluation

For the cost-effectiveness analysis, we will empirically quantify the incremental cost-effectiveness ratio (ICER) for the cost per additional facility-based delivery and per additional ANC visit. We will calculate the total healthcare expenditure during pregnancy, delivery, and neonatal period to calculate the incremental costs, which will be divided by the primary outcomes (i) facility-based delivery and (ii) ANC visits. Furthermore, we will calculate ICER with DALYs as denominator by using the standard DALY formula by limiting the disabilities caused by the most common and life-threatening obstetric complications (postpartum hemorrhage, obstructed labor, puerperal sepsis, preeclampsia/eclampsia, and asphyxia) [60–62]. In a second step, we will assess the robustness of the cost-effectiveness analysis by applying a sensitivity analysis. For the quantification of financial distress, we consider the cumulative number of patients reporting at least one of the following signs of financial distress due to maternal and neonatal healthcare costs: (i) assets sold or money borrowed, (ii) relative or friend asked to pay, (iii) catastrophic healthcare expenditure of more than 10% of annual household income, and (iv) essential healthcare forgone because of expected expenditure. All local costs will be calculated in Malagasy Ariary (MGA) before conversion to US dollars (USD) using the average annual exchange rate. Costs and health effects will be discounted and inflation-adjusted using the average consumer price index during the study period. We will use the market price for salary and utility grid to value the additional workload.

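### Time to seek medical attention has no value for women who never accessed care, so the stated linear regression compares groups selected after randomisation, with bias of uncertain sign

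*Protocol article*

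**What the plan says.** Table 1 defines time to seek medical attention as "Time from first symptoms until professional medical care was accessed", types it as "Continuous time variable", takes it from the household survey and marks it as pre-registered.

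The section on analysis of the randomized controlled trial applies one scheme to the whole table: "We will regress the primary and secondary outcomes (Table 1) on the random assignment of participants to facility catchment intervention vs. control area". The model follows from the variable type: "for our continuous outcomes, we will use linear regression for effect size estimation". The estimand is also stated: "Our primary analysis will be an intent-to-treat (ITT) causal effect estimation of our registered pre-specified primary and secondary outcomes". So is the property claimed for it: "The effect sizes determined in the primary analysis provide an unbiased measure of the real-life policy impact of our intervention".

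Two other places bear on whether women who never reach care will exist and differ between arms. The conceptual framework hypothesises that the wallet "will improve access to skilled care during pregnancy and childbirth by reducing financial obstacles". The economic evaluation lists among the signs of financial distress "essential healthcare forgone because of expected expenditure".

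**The concern.** A duration that ends at access does not exist for a woman who had symptoms and never accessed care. Ordinary linear regression has no means of handling a duration that was never completed. Unless a value is assigned to her, and the article names none, she leaves the analysis.

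Her leaving is not ignorable. Whether a symptomatic woman reaches care is settled after randomisation, and raising that proportion is the purpose of the intervention. If it succeeds, the intervention arm's analysed set contains women whose counterparts in the control arm are absent. Randomisation no longer protects the comparison, and the difference in means mixes two things: a change in delay among women who would have come anyway, and a change in who is counted. At stake is the reading of one registered outcome, where a real improvement could be hidden or shown as longer delay, or a null effect could look like an improvement.

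**Working it through.** **No figure to reproduce.** The article gives no mean, standard deviation, power or access proportion for this outcome. All sizes below rest on assumed inputs.

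**Notation.** p_C and p_I are the proportions of symptomatic women accessing care in control and intervention; m_C is the control mean delay among them; r is the true time ratio in women who would access care in either arm; a is the mean delay of the added women. Nobody is assumed to be deterred by the intervention.

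**Analysed intervention mean**

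m_I = [p_C × r × m_C + (p_I − p_C) × a] / p_I

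**Bias relative to the true effect in existing seekers**

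m_I − r × m_C = [(p_I − p_C) / p_I] × (a − r × m_C)

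The sign is therefore the sign of (a − r × m_C): positive if added women are slower than existing seekers, zero if equal, negative if faster.

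**Assumed inputs.** p_C = 0.60 and m_C = 2.0 days. The access gain is 4 points (borrowed in scale from the facility-delivery difference under Power calculation) or 10 points (assumed). Added women arrive at 5 days, at 2.0 days (equal to controls) or at 1.0 day (half of controls).

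With arrivals at 5 days:
- 4 points, r = 1: (0.60 × 2.0 + 0.04 × 5) / 0.64 = 1.40 / 0.64 = 2.19
- 10 points, r = 1: (1.20 + 0.50) / 0.70 = 2.43
- 4 points, r = 0.9: (0.60 × 1.8 + 0.20) / 0.64 = 1.28 / 0.64 = 2.00
- 10 points, r = 0.9: (1.08 + 0.50) / 0.70 = 2.26

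The same formula gives the other columns (analysed intervention mean in days, against a control mean of 2.00):

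| Access gain | Existing seekers | Added at 1.0 day | Added at 2.0 days | Added at 5 days |
|---|---|---|---|---|
| 4 points | unchanged | 1.94 | 2.00 | 2.19 |
| 10 points | unchanged | 1.86 | 2.00 | 2.43 |
| 4 points | 10% faster | 1.75 | 1.81 | 2.00 |
| 10 points | 10% faster | 1.69 | 1.83 | 2.26 |

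**Second set of inputs.** Take 74% as p_C, the regional share with qualified help at birth under Study setting. It is only a proxy for access after symptoms. Write k for the added women's delay relative to control accessors. The apparent time ratio is [0.74 × r + (p_I − 0.74) × k] / p_I. With p_I = 0.78 and r = 1, it is 0.97, 1.00, 1.05 and 1.10 for k = 0.5, 1, 2 and 3. With r = 0.95 and k = 2 it is (0.703 + 0.08) / 0.78 = 1.004, so a true 5% speed-up is fully masked.

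**Simulation.** Let every woman have a latent delay (lognormal, median 2 days, log-SD 1, both assumed), with care never reached beyond the point at which 74% of controls have arrived. True time ratios of 0.90, 0.80 and 0.70 appear as 0.96, 0.91 and 0.85 among accessors only, against 0.94, 0.88 and 0.81 by restricted mean over all women. Here the effect is attenuated, not reversed.

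**What the fix does.** Cap time at a horizon H that lies beyond all arrivals, and give H to women who never accessed care. In the first example with r = 1, the control mean is 1.20 + 0.40H and the intervention mean for a 4-point gain is 1.20 + 0.20 + 0.36H. The difference is −0.04 × (H − 5), which is negative for any H above 5 days. For 10 points it is −0.10 × (H − 5). Bringing more women to care then counts as an improvement.

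**The case against.** The article does not say in words that the regression is limited to women who accessed care. A cap, a censoring rule or an imputed value could sit in a questionnaire or an analysis plan that is not shown, and an article may leave such detail out. This stands as a limit on certainty. It does not remove the point: definition, variable type, model and claimed property are all stated, and applied together they yield a selected comparison. A survival analysis would depart from the stated rule.

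Nor is linear regression itself the fault. The survey looks back, so time capped at a short horizon is known for nearly every woman with symptoms, and regressing it on assignment estimates a restricted-mean difference. This stands and is reflected in the fix.

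A reader might infer that the analysis is biased against the intervention and will make benefit look like harm. The documents do not support that. No delay data are given, and the package includes round-the-clock emergency referral and active follow-up by dedicated health workers, so added women need not be late. With a 10% speed-up and a 10-point gain, arrivals at 3 days give (1.08 + 0.30) / 0.70 = 1.97 days, a small apparent benefit.

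Finally, access is partly captured elsewhere, through facility delivery, ANC visits and the forgone-care item. And the set of women reporting symptoms is itself formed after randomisation: counselling, ultrasound and staff training may change what is recognised. Both stand; the second limits any remedy.

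**Conclusion.** The point holds as a selection bias of uncertain sign. As written, the outcome exists only for women who accessed care, the model is fixed, and the result is described as an unbiased intention-to-treat effect. That description is not tenable for this outcome if access differs by arm, which the trial hypothesises. It rests on two assumptions: that no value is assigned to symptomatic women who never accessed care, and that such women exist, which the forgone-care item implies.

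The size cannot be established from the article. In the 60%, 2.0-day and 5-day illustration, the distortion with no true change in existing seekers is 0.19 days (4 points) to 0.43 days (10 points). A true 0.2-day speed-up is cancelled at 4 points and appears as a 0.26-day worsening at 10 points. With equally fast added women and no change in existing seekers the distortion is nil; with faster ones it changes sign. Late arrival of cost-deterred women is plausible but not shown. The primary outcomes are unaffected.

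**What to change.** Define the analysis population as all women reporting symptoms, and count those who never accessed care. Either of two analyses would serve, each with cluster-robust standard errors:

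- time-to-event from first symptoms, with women who never accessed care censored at a stated follow-up point; or
- restricted mean time, with time capped at a fixed horizon stated in advance. Linear regression is acceptable here wherever the capped time is known.

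Report by arm the proportion of symptomatic women who accessed care and the proportion of all women reporting symptoms. State that symptom reporting may itself be affected by the intervention, so even the corrected comparison is not fully protected by randomisation.

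The cost is analysis wording and, if the questionnaire does not already have it, one item on whether care was ever accessed. The article places outcome assessment from January 2022, after trial registration in March 2021, so as of the article this could be settled before data collection. No extra participants are needed.

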## Methods

### Study setting

We will conduct this study in the health districts Antananarivo North (Avaradrano), Centre (Renivohitra), and South (Atsimondrana) within the region of Analamanga, Madagascar. The districts are urban, peri-urban, and rural and include Antananarivo, the capital of the country. The study region has 2.2 million inhabitants, 31% of whom live under the national poverty line (535,603 Malagasy Ariary per capita income; 248.42 USD, 2011 PPP), considerably less than the Malagasy average (71%) [32, 42]; 77.4% of the Malagasy population live below the international poverty line of 1.9$ per day (2011 PPP) [43]. The lingua franca is Malagasy. In the study region Analamanga, 65% of pregnant women complete at least 4 ANC visits, 68% deliver at a public or private health facility while 74% have qualified assistance during birth [34]. Public healthcare in these districts is provided by 65 public-sector health facilities, comprising 61 primary-care health facilities (“Centre de santé de base”) and four public reference hospitals for maternal healthcare. Primary-care health facility staff includes at least one doctor and two midwives or nurses. Each primary-care health facility has approximately 15–30 affiliated community health workers (CHWs) who advise pregnant women to seek ANC at the primary-care health facility [44]. In addition, CHWs provide information on general health aspects, possible complications, and nutrition during pregnancy. Each of the primary-care health facilities in the study region performed between 40 and 5437 prenatal examinations and 0 to 1150 deliveries in 2017. If complications occur or more specific treatment is required, primary-care health facilities can refer patients, at the patient’s expense, to a reference hospital. ANC, vaginal and C-section deliveries as well as accommodation are free of charge for patients at primary-care health facilities and reference hospitals. However, any medication, lab tests or materials required for delivery or surgery must be purchased in cash by patients from the pharmacy, which is affiliated with a health facility. A vaginal delivery without complications costs on average about 12 USD and a C-section costs around 128 USD in total, representing 3% and 32% of the average annual salary in the region, respectively [45–47].

### Study design

We will conduct this trial comparing the intervention package to the usual standard of care in 61 public-sector primary-care health facilities—randomized by 6 strata—in Madagascar’s Analamanga region. We selected a hybrid effectiveness-implementation type-1 design, because it blends design components of a cluster-randomized impact evaluation and mixed-methods evaluation to inform future implementation efforts [48]. This trial complements an intervention which was co-created with the Malagasy Ministry of Health and implemented by a non-governmental organization. The motivation for facility randomization was the need to ration the intervention to selected facilities due to the implementer’s funding constraints. Randomization allowed for the unbiased allocation of facilities to the intervention or control group free from political or logistical reasons while ensuring procedural equality [49]. After intervention implementation, it became clear that a scientific evaluation would be feasible allowing for strong causal inference of the effect of the intervention. Thus, trial registration occurred after randomization and intervention implementation on March 12, 2021, but before the initiation of outcome assessment. This manuscript complies with the SPIRIT checklist (see Additional file 2) [50].

### Eligibility criteria

#### Clusters

All public-sector primary-care health facilities that perform ANC in the study region were eligible for randomization (Fig. 1).

**Fig. 1 Fig1:**
[figure not shown]
Public-sector primary-care health facilities and reference hospitals in Antananarivo Atsimondrana (South), Renivohitra (Centre), and Avaradrano (North) health districts in Analamanaga region, Madagascar

#### Inclusion criteria

All young mothers who lived in a randomly selected census enumeration area within the catchment area of a primary-care health facility participating in this study and who completed their pregnancy between July 1, 2020, and December 31, 2021, will be asked for their verbal consent to participate in the study. Participants must be able and willing to give verbal consent for trial participation; they must be at least 18 years old to participate. Providers will be eligible to be included in the study if they are working within a facility where the study is taking place and are at least 18 years old.

#### Exclusion criteria

Individuals considered unable to provide and participate in informed consent including those with uncontrolled psychiatric disorders or severe neurological impairment resulting in an inability to participate in the informed consent process.

### Procedures

#### Intervention package

The intervention package examined in this study consists of three elements: (i) the MMHW for restricted health savings during pregnancy, (ii) conditional cash transfers and electronic vouchers for maternal and neonatal healthcare services and emergency evacuation, and (iii) quality of care assessments and trainings for facility-based health workers. The intervention package is implemented by a non-governmental organization in partnership with the Malagasy Ministry of Health’s UHC program. Sequential implementation of the intervention package commenced in January 2019 and all randomized facilities received the intervention at least since May 2020.

#### Mobile Maternal Health Wallet

The core system behind the MMHW is a software that allows users to pay for maternal healthcare services using MM at participating health facilities in return for treatment-related data being provided by the health facility to the MMHW service provider. On the user’s side, the MMHW is an unstructured supplementary service data (USSD) menu, which is accessible through the Global System for Mobile communication networks (GSM) of the two major Malagasy mobile phone operators by dialing a 3-digit number followed by the hash sign. Thus, using the MMHW does not require an active internet connection or smartphone capabilities. Users can save to the MMHW using their own MM credit or by receiving remittances via MM from relatives and friends. At the health facility level, health workers use a web-based interface to initiate and validate payments by entering a unique transaction authentication number (TAN) and uploading supporting documents such as a photo of the invoice. Semi-automated plausibility checks are performed upon each payment request to protect participants from fraud. Funds remaining on the MMHW are credited to the user’s regular MM account after delivery or at any time prior to completion of the pregnancy if a participant chooses to end her MMHW membership.

#### Restricted cash transfers and electronic vouchers

To incentivize users to save for perinatal medical expenses, each amount credited to the MMHW is topped up with a bonus of 50% of the saved amount. This bonus can only be used to pay for maternal healthcare services; it is not credited to a user’s MM account upon completion of the pregnancy or if a participant chooses to end MMHW membership. In addition, upon sign-up and corresponding to current WHO recommendations, users receive electronic vouchers for free-of-charge (i) ANC drugs such as iron and folic acid supplements; (ii) at least one prenatal ultrasound exam taking place before the 20th week of pregnancy and subsequent follow-up ultrasound exams if medically indicated; and (iii) emergency treatment and referral from a primary-care health facility to a reference hospital in case of a medical emergency during pregnancy or childbirth. Users are informed about their eligibility for conditional cash transfers and electronic vouchers by health workers and automated SMS messages. Users can redeem vouchers for ANC drugs at pharmacies of participating health facilities; ultrasound exams are performed by midwives specialized in prenatal ultrasound at participating health facilities at least once a month, and emergency services can be requested 24/7 by health workers using a Toll-free number. Once a new user has registered for the MMHW and before being eligible to receive restricted cash transfers or electronic vouchers, the account is validated by a facility-based health worker or dedicated MMHW health worker by uploading a photo of the user’s ID card or proof of residence using the MMHW’s web-based interface.

